**Medication of the study. Compliance surveillance**

The medication will be administered from the Pharmacy service of the hospital itself. An empty blister count and interview with the patient will be performed to monitor compliance.

## Statistic analysis

**Sample size estimation**. Taking into account the current high prevalence of infection in healthcare personnel in Spain (up to 15%), to detect a difference equal to or greater than 8% in the percentage estimates through a two-tailed 95% CI, with a statistical power of 80% and a dropout rate of 5%, a total of 450 participants will need to be included (250 in each arm).

## Data Collect. The data collection will be carried out by the researchers assigned to it by means of a data collection notebook designed for it. This notebook will have a digital format and will be designed by the main researcher. This study proposes a prospective collection of information, so that data will be obtained through scheduled visits. Information sources include the patient's medical history and information provided by the physician. Each participant will be assigned a code that does not allow them to be directly identified. The relationship between the codes and the identity of the subjects will be guarded by the research team. The latter will be responsible for preserving the information. At all times the current regulations on personal data protection and guarantee of digital rights will be followed. (See later)

# **General considerations of statistical analysis.** The data will be analyzed using the SPSS version 21 program. A descriptive analysis will be performed at baseline and at the end of the follow-up (week 96) of the data using mean and standard deviation or median and range when necessary for quantitative data and percentage for qualitative data. The quantitative variables will be compared with t-student and the qualitative variables will be compared with X2. When the variables do not follow a normal distribution, non-parametric tests will be used. Prevalence, cumulative incidence, and incidence rate will be determined with their 95% confidence intervals by standard methods. Paired data tests will be used to analyze baseline results and end of treatment.

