**TITLE:** Controlled, double-blind, randomized trial to assess the efficacy and safety of hydroxychloroquine chemoprophylaxis in SARS CoV2 infection in healthcare personnel in the hospital setting (SANsinCOVID).

**Promoter:** Instituto de Investigación Valdecilla (IDIVAL)

**Code:** SANsinCOVID

**EudraCT:** 2020-001704-42

**Main investigators:** [name]. Jefe Servicio Digestivo

[name]. Jefe Servicio Infecciosas

**Collaborating investigators:** [name]. Jefe Servicio Medicina Interna

[name]. Jefe Servicio Neumología

[name]. Jefe Servicio Preventiva.

[name]. Jefe S. Riesgo Laborales

[name]. Jefe Servicio Inmunología

[name]. Reumatología

[name]. Servicio Farmacia Hospitalaria

**Funding:** This study has no source of funding.

**Contact:** - Clinical Research and Clinical Trials Unit Marqués de Valdecilla University Hospital

- [name].

- Santander Tel .: [name] [contact]

- Email: [[contact]](mailto:[contact])

1. **Summary**

Health professionals have a high risk of SARS CoV2 infection as evidenced by the data observed in China, Italy and Spain (about 10,000 at the moment, 12-15% of all registered cases, data from the Ministry of Health). This risk is higher in professionals who work in high risk areas where aerosols can be produced. Hydroxychloroquine (HDQ) has been shown to inhibit coronavirus in vitro, although very little clinical results are available. HDQ is a widely used, low-cost, limited-toxicity drug. Currently, there is no type of exposure prophylaxis that has proven to be useful against SARS CoV2. For this reason, we intend to develop a randomized, double-blind, controlled clinical trial with two parallel groups (200 mg of HCQ per day versus placebo) with a prophylaxis duration of 60 days.

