**Case definition:**

**1) Symptomatic case:** Symptomatic COVID-19 infection defined as cough, dyspnea, fever, myalgia, arthralgia or rhinorrhea plus SARS Cov2 positive PCR.

**2) Asymptomatic case:** SARS Cov2 PCR in the absence of any symptoms potentially related to COVID19.

**3) Case cured:** IgG serology positive with SARS Cov2 negative PCR and absence of symptoms (this HP will be excluded, but gives valuable information on the prevalence of infection in HP).

**Study duration:** Twenty-five weeks, distributed as follows: 1) Recruitment period: Eight weeks from the inclusion of the first subject to the inclusion of the last study individual. 2) Screening period: After signing the informed consent, an IgG serology and coronavirus PCR will be performed, the result of which will be obtained in a maximum period of 7 days. After obtaining a negative result and corroborating a non-prolonged QTc interval, the study subject will start taking the corresponding medication. 3) Eight weeks of chemoprophylaxis vs placebo. 4) Eight weeks for database debugging and analysis of results. Preliminary publication of the first results.

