**Questionnaire and variables to analyze.** Demographic data. Profession (assistant, technician, caretaker, nurse, doctor). Specialty and definition of the job. Follow-up of the recommendations (use of PPE, hand hygiene). Definition and history of the type of contact (s): 1) Close contact with possible, probable or confirmed case with required PPE use. 2) Close contact with possible, probable or confirmed case without use of required PPE. 3) Casual contact with possible, probable or confirmed case with the use of required PPE. Comorbidities (HT, DM, Smoker, Pulmonary, cardiac pathology). Pharmacological treatment at the time of inclusion in the study. Information about the COVID19 infection if it occurs (date of diagnosis). **Analytical evaluation:** Leukocyte count, platelets, hemoglobin, prothrombin activity, INR, urea, creatinine, glucose, cholesterol, HDL, LDL, AST, ALT, alkaline phosphatase, GGT, bilirubin, albumin, sodium, potassium, prothrombin rate, proteins totals, triglycerides, ferritin, uric acid, PCR. **Electrocardiogram. A sample for research** will be obtained at baseline and + 10 weeks, which will be transferred and stored in the Biobank for future research in the line of research; one of the samples will include DNA. **Clinical manifestations:** cough, odynophagia, fever, dyspnea, pleuritic pain, headache, diarrhea, anosmia, ageusia, others. **Severity:** qSOFA scale, CURB-65, evolution to ARDS, need for mechanical ventilation. Radiological manifestations. **Treatment** of the infection**. Evaluation of the adverse effects** of the administered medication**.**

**Main outcomes**The primary outcome of this study will be to evaluate:

Number and percentage of subjects presenting symptomatic and asymptomatic infection (see “Diagnosis of SARS CoV2 infection” below) by the SARS-Cov2 virus during the study observation period (8 weeks) in both treatment arms.

Number and percentage of subjects in each group presenting Pneumonia with severity criteria (Curb 65 ≥2) and number and percentage of subjects requiring admission to the Intensive Care Unit (ICU) in both treatment arms

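### The only stated test for the infection endpoint is an unadjusted chi-squared; a small prespecified baseline adjustment, reported as a risk difference with CI, would use data already collected

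*Protocol*

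**What the plan says.** - **Test.** Under General considerations of statistical analysis, the protocol says that "the qualitative variables will be compared with X2". The t-test and non-parametric alternatives are for quantitative data, and the paired tests compare baseline with end of treatment. Chi-squared is therefore the only between-arm method that fits the infection outcome listed under Main outcomes. No covariate or adjusted model is named.
- **Intervals.** The same section promises 95% intervals for prevalence, cumulative incidence and incidence rate. It names no between-arm difference. Sample size estimation, by contrast, plans "to detect a difference equal to or greater than 8" percentage points "through a two-tailed 95% CI".
- **Predictors.** The Summary states: "This risk is higher in professionals who work in high risk areas where aerosols can be produced". Questionnaire and variables to analyze records profession, job, PPE use, hand hygiene and contact type, including "Close contact with possible, probable or confirmed case without use of required PPE".
- **Entry.** Study duration sets recruitment at "Eight weeks from the inclusion of the first subject to the inclusion of the last study individual".
- **Allocation.** Study design describes a computer-generated random sequence at 1:1 and mentions no strata.

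**The concern.** The protocol itself ties infection risk to exposure, records exposure, and enrols over two months of an epidemic. With no strata in the randomisation, chance imbalance in exposure between arms is left in the comparison. Adjusting for values fixed before randomisation removes that imbalance and usually tightens the estimate, with no extra participants.

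Precision matters here because 225 per arm is already short of the stated 80% power. A chi-squared p-value also does not give the quantity on which the trial was sized, the difference in infection percentages with its interval.

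**Working it through.** **Inputs from Sample size estimation:** two-sided 5%, power 80%, control risk up to 15% (15% used), difference 8 points (so 15% against 7%), dropout 5%. **From Study design:** 225 per arm.

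**The plan's own figure.** With p̄ = 0.11, √(2p̄q̄) = √0.1958 = 0.4425 and √(p₁q₁+p₂q₂) = √0.1926 = 0.4389:

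n = [(1.960 × 0.4425 + 0.842 × 0.4389) / 0.08]² ≈ 239 per arm; 239/0.95 gives 252.

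The unpooled formula gives 237, then 250. So 250 per arm (500 in total) reproduces and 450 in total does not.

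**Power of chi-squared as planned.** Evaluable n = 225 × 0.95 = 213.75 per arm.

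Power = Φ[(0.08√n − 1.960 × 0.4425)/0.4389] = Φ[(1.1696 − 0.8673)/0.4389] = Φ(0.689) = 75.5%. Without dropout it is 77.6%.

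Expected infections: 213.75 × (0.15 + 0.07) ≈ 47.

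**Effect of adjustment.** If adjustment cuts the variance by a fraction V, the effective n is 213.75/(1 − V). Reaching 239 needs V = 1 − 213.75/239 = 10.6%, equivalent to about 478 − 427.5 ≈ 50 more evaluable participants.

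**What V might be.** The documents give no prognostic strength, so the relative risks below are assumptions. Trials of 428 participants were simulated, 3,000 per scenario, comparing chi-squared with a standardised risk difference from logistic regression. Each scenario was simulated twice, independently.

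| Assumed predictors (cumulative) | Variance cut (two runs) | Power by formula (first run's cut) | Simulated power, chi-squared → adjusted (two runs) |
|---|---|---|---|
| Work area, RR 2 | 0.1%; about 0% | 75.5% | 76.0→76.8; 77.0→77.8 |
| + unprotected contact, RR 3 in 20% | 4.3%; 4.8% | 77.3% | 74.5→76.5; 75.8→77.8 |
| + 4-fold risk change over enrolment | 7.1%; 7.8% | 78.5% | 76.3→80.2; 76.1→80.1 |
| + 10-fold risk change | 12.2%; 12.8% | 80.7% | 76.5→81.6; 74.5→80.8 |

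The simulated gains exceed what the variance cut implies: even the 0.1% row shows 0.8 points. Part of this is simulation error, about √(0.76 × 0.24/3000) = 0.8 points on each power figure. Part may be the different test, since null rejection in the first run was 4.8–5.1% adjusted against 4.4–4.9% for chi-squared. The formula column is the safer guide.

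**Size of model.** Three covariate terms plus treatment leave 47/4 ≈ 12 events per coefficient; ten plus treatment leave 47/11 ≈ 4. In further simulations (428 participants, 2,000 runs per scenario), a two-term adjustment cost about nothing when the terms did not predict and cut variance by about 1–9% when they did. A ten-covariate model could raise variance by about 3%, with null rejection up to 5.5%.

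**The case against.** The strongest case is that nothing here is wrong.

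- **The SAP may deal with it.** The test sits under general considerations and is not called the primary analysis. Covariate adjustment is commonly left to an SAP, which is not available here. This stands in part. An SAP may refine the method, but the protocol does state one for this kind of outcome, and it is unadjusted.
- **Chi-squared is valid.** This stands fully. A reader might infer that a changing epidemic biases the comparison. It does not: arms are randomised concurrently, so calendar time affects precision only.
- **The predictors may be weak.** This stands. A reader might infer strong predictors from the protocol's remarks on exposure, but it gives no effect sizes and no incidence trend. Eligibility is already limited to high-exposure work, which narrows the work-area contrast. The larger gains also need steep trends: with a mean control risk of 15%, a linear 4-fold change runs between 24% and 6%, and a 10-fold change between about 27% and 3%.
- **Timing is unclear.** This stands. The questionnaire text does not say when PPE use and contact history are recorded. Inclusion criterion 3 does refer to work in the preceding two weeks, so a pre-randomisation exposure window exists.
- **Intervals are partly planned.** This is true for incidence estimates, but not for the between-arm difference in the analysis section.

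**Conclusion.** The point holds as an optional improvement in efficiency. The stated analysis is valid but leaves recorded baseline information unused, and the analysis section omits the between-arm difference on which the trial was sized.

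The size of the gain rests on assumed prognostic strengths. Across the scenarios the variance cut is 0% to about 12%, taking power by formula from about 75.5% to at most about 81%. Only the most extreme scenario passes the 10.6% needed for 80%.

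A reader might conclude that adjustment repairs the power shortfall. The documents do not support that: the shortfall comes from enrolling 225 per arm when the protocol's own inputs lead to about 250, and adjustment does not reconcile those figures. All power figures also assume a 15% control risk, which the protocol gives as an upper value. At the same relative reduction, unadjusted power is 56.2% with a 10% control risk.

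**What to change.** Before unblinding, prespecify as primary analysis a covariate-standardised risk difference with 95% CI and robust standard error. Obtain it from a logistic model averaged over all randomised participants.

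- Include treatment plus two or three terms fixed before randomisation: for example, a two-level baseline exposure or contact category, and calendar time of entry as a linear term.
- Exclude PPE use and contacts recorded after randomisation. State when the baseline questionnaire is completed.
- Define any merging of sparse categories in advance, given about 47 expected events.
- Keep chi-squared as a supporting analysis.

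The cost is a change of wording and slightly more programming, with no new data or visits. If the covariates do not predict infection, the loss from so small a model is negligible. Correct the contradiction between 450 in total and 250 per arm separately.

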**Secondary objectives.**

2) To assess the safety of HDQ for 2 months in healthcare personnel.

3) To evaluate the number of working days lost as a result of symptomatic or asymptomatic infection with COVID19.

4) To analyze the percentage of severe respiratory disease by COVID-19 in healthcare personnel.

5) To define the incidence, prevalence and severity of SARS CoV-2 infection in healthcare personnel in the hospital setting.

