**Methodology. Design, study subjects, variables, data collection and analysis, and study limitations.**

**Study design.** Prospective, randomized and placebo-controlled clinical Trial. The medication will be manufactured in the Pharmacy of the Marqués de Valdecilla University Hospital (HUMV). Two groups will be analyzed with a 1: 1 randomization. The allocation to both arms will be done through the generation of a sequence of random numbers by computer. Chemoprophylaxis group (n = 225): One 200 mg HDQ tablet once daily for two months. Control group (n = 225): One placebo tablet (identical to that of the drug) once a day for two months.

**Study population.** It will include 450 health professionals who are working in areas of high exposure and high risk of transmission of SARS CoV2 (professionals from the Hospital in COVID areas, Intensive Care Unit, Emergencies, Anesthesia and all those who carry out procedures that generate aerosols).

**Inclusion criteria:** 1) Health professional aged between 18 and 65 years (inclusive) at the time of the first screening visit. 2) They must provide signed written informed consent and agree to abide by the study protocol. 3) Active work in high exposure areas during the last two weeks and during the following weeks.

**Exclusion criteria:** 1) Previous infection with SARS CoV2 (positive coronavirus PCR or positive IgG serology with SARS Cov2 negative PCR and absence of symptoms). 2) Current treatment with HDQ or chloroquine. 3) Contraindication for taking HCQ (known epilepsy, porphyria, recent ischemic heart disease). 4) Previous or current treatment with tamoxifen or raloxifene. 5) Previous eye disease, especially maculopathy. 6) Known heart failure (Grade III to IV of the New York Heart Association classification) or prolonged QTc. 7) Any type of cancer (except basal cell) in the last 5 years. 6) Refusal to give informed consent. 8) Evidence of any other unstable or clinically significant untreated immunological, endocrine, hematological, gastrointestinal, neurological, neoplastic or psychiatric illness. 9) Antibodies positive for the human immunodeficiency virus. 10) Significant kidney or liver disease. Pregnancy or lactation; Hypersensitivity or allergy to HQ, cq contraindication in data sheet to taking HQ.

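### Paired tests are the only method named for baseline versus end-of-treatment results, and a paired test does not compare hydroxychloroquine with placebo

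*Protocol*

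**What the plan says.** The protocol describes its design as "Prospective, randomized and placebo-controlled clinical Trial" and adds that "Two groups will be analyzed with a 1: 1 randomization".

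Under 'General considerations of statistical analysis', two sentences bear on quantitative variables:

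- "The quantitative variables will be compared with t-student and the qualitative variables will be compared with X2". Non-parametric tests follow if normality fails. The groups being compared are not named, nor is it said whether the variable is the end value or the change.
- "Paired data tests will be used to analyze baseline results and end of treatment". No arm, no variable and no rule of interpretation is given.

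The variables to which the second sentence most plausibly applies are in the analytical evaluation listed under 'Questionnaire and variables to analyze', which begins "Leukocyte count, platelets, hemoglobin, prothrombin activity, INR, urea, creatinine, glucose" and runs to 25 items by count. That list carries no time points.

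Among the secondary objectives is "To assess the safety of HDQ for 2 months in healthcare personnel". The section 'Security analysis' provides for lists of adverse events by study group and a descriptive analysis in each group.

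**The concern.** A paired test asks whether values moved between two visits. The question in a placebo-controlled trial is whether they moved more on the drug than on placebo. Season, workload and regression to the mean can shift laboratory values in both arms over two months, and a paired test cannot separate such a shift from a drug effect. The placebo group can, but only if the analysis compares the arms.

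Two things are at stake, both for secondary quantitative data. First, the only method tied to baseline and end-of-treatment results leaves the control group out. If it is run separately by arm, a reader of the results may set a significant arm beside a non-significant one and take the difference for an effect. Second, if the t-test is applied to end values alone, baseline values that the plan implies are collected do nothing for precision.

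**Working it through.** The protocol gives no figure for the paired tests, so there is none to reproduce. The check asks what follows from the named method.

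**Inputs**

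- Participants per arm: 225 (design section). The sample-size paragraph gives a different per-arm number. That is a separate matter, and the ceiling in step 2 does not depend on it.
- Dropout: 5% (sample-size paragraph). 225 × 0.95 = 213.75, taken as 213 completers per arm.
- Two-sided 5% level.
- Assumed, because the protocol gives no standard deviations: normally distributed changes with equal SD in both arms, and a true mean change *d* (in SDs of the change) that is the same in both arms. The drug therefore has no effect. *d* is shown over a range.

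**Step 1. Does either reading of the sentence compare the arms?**

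- Within each arm: each test estimates drug effect plus drift in one arm, and drift alone in the other. Neither test estimates the difference.
- Pooled: the test estimates the average change over both arms. It has no treatment term.

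The answer is no on both readings. The one-arm-significant pattern can arise only on the first.

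**Step 2. How often would separate tests mislead?**

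Let *w* be the power of the paired t-test in one arm (noncentral t, 212 df, noncentrality *d*√213). The arms are independent, so

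P(only the hydroxychloroquine arm has p<0.05) = *w*(1 − *w*).

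| Shared drift *d* | *w* | Hydroxychloroquine arm only |
|---|---|---|
| 0 | 0.050 | 0.050 × 0.950 = 4.75% |
| 0.05 | 0.112 | 10.0% |
| 0.10 | 0.306 | 0.306 × 0.694 = 21% |
| 0.134 | 0.495 | 0.495 × 0.505 = 25% |
| 0.20 | 0.828 | 0.828 × 0.172 = 14% |
| 0.30 | 0.992 | 0.8% |

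The product *w*(1 − *w*) cannot exceed 0.25 at any sample size. The sample size only sets the drift at which the ceiling is reached. Placebo-only results are equally likely, so exactly one arm is significant in twice these proportions: 9.5% at no drift, 42.5% at 0.10 SD and 50% at 0.134 SD.

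**Step 3. The direct comparison.** In a two-sample t-test on change the shared drift cancels. In 20,000 simulated trials at *d* = 0, 0.134 and 0.20 it was significant in 4.8% to 5.1%. The same simulations gave hydroxychloroquine-only results in 4.9%, 25.3% and 14.3%, in agreement with the table.

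**Step 4. Precision.** With a baseline-to-end correlation ρ, the variance of the ANCOVA treatment estimate relative to a t-test on end values is 1 − ρ².

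- ρ = 0.5: 1 − 0.25 = 0.75, a cut of 25%.
- ρ = 0.7: 1 − 0.49 = 0.51, a cut of 49%.

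If the t-test were applied to changes instead, and the variance is equal at both times, the ratio is (1 − ρ²)/(2(1 − ρ)) = (1 + ρ)/2. That is 0.75 at ρ = 0.5 and 0.85 at ρ = 0.7, or cuts of 25% and 15%. Both correlations are assumed.

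**The case against.** The strongest reply is that the paragraph already contains a comparison of the arms. In a two-group trial the Student t sentence most naturally means drug against placebo, and the paired sentence stands beside it without replacing it. An unadjusted t-test in a randomised trial is valid, and on change scores it holds its level whatever the drift. Covariate adjustment for secondary laboratory variables is often left to a statistical analysis plan. This largely stands, and it limits the point. It does not remove it: for baseline and end-of-treatment results the protocol does fix a method, and the method it fixes has no treatment contrast.

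A reader might go further and infer any of the following. The protocol does not support them.

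- *That significance in one arm only will be read as a drug effect.* The protocol never says this, nor that the tests are run by arm. Step 2 of the working is therefore conditional on a use that the text permits but does not plan.
- *That the safety conclusion rests on these tests.* Adverse events are described by study group, and Annex 1 counts an abnormal laboratory finding as a possible adverse event. No section bases a safety conclusion on paired tests.
- *That the panel is scheduled at baseline and end of treatment.* This is inferred from the paired-test sentence. The baseline and week-10 samples in the protocol are for the Biobank.
- *That the false-signal rate is 43% to 50%.* Those figures count placebo-only results and rest on assumed drifts. A spurious signal for the drug is half as frequent. With no drift it is 4.75%, or 25 × 0.0475 ≈ 1.2 of 25 laboratory values, no more than a direct test at 5% would give.

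**Conclusion.** The point holds in a limited form. The only method named for baseline versus end-of-treatment results does not compare hydroxychloroquine with placebo on either reading, and the accompanying t-test states no baseline adjustment. The primary outcomes (infection, severe pneumonia, ICU admission) are numbers and percentages by arm and are untouched.

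Misreading separate within-arm tests would produce a hydroxychloroquine-only signal in somewhere between under 1% and 25% of null comparisons, depending on a drift that the protocol gives no means of estimating. Excess false signals arise only for intermediate drifts: of the values tabulated, 0.05 to 0.20 SD. The precision gain from adjustment depends on the assumed correlations and on which quantity the t-test would have used. This is a worthwhile improvement to secondary analyses, not a threat to the trial's main conclusion.

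**What to change.** Replace the paired-test sentence under 'General considerations of statistical analysis' with:

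> End-of-treatment quantitative values will be compared between arms by ANCOVA with the baseline value as covariate (log-transformed where skewed), reporting the adjusted difference and 95% CI; within-arm changes will be described without being used to infer a drug effect.

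The cost is wording only, provided that the variables are measured at both times, as the present sentence implies. No new visits or participants are needed, and ANCOVA is available in the software that the protocol names. The change should be made before unblinding.
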